### 2.2. Context

GAME is a non-profit organisation founded in 2002 with the objective of creating lasting social change through peer-led street sport and culture. One of GAME’s target areas is low resource neighbourhoods [28]. In Denmark, low resource neighbourhoods are defined based on employment rates, educational level, and criminal conviction rates among residents relative to the general population [29]. Street sport is characterised as sport activities, held in urban environments, of a non-commercial and non-professional nature (e.g., street basket, street soccer or street dance) [30]. The three main features of GAME’s programme are (1) a peer-to-peer approach in which local voluntary peer-leaders aged 16–25 years (Playmakers) are trained and supported in being role models and lead weekly diverse street sport activities for children aged 8–15 years (participants) living in low resource neighbourhoods. (2) Street sports activities are free of charge for children and do not require formal approvement by parents for children to participate. (3) The Playmakers are trained to conduct street sport activities that are inclusive and builds life skills and positive social relations among participants. In Denmark, GAME’s involvements range from neighbourhoods with one activity with few participating children to neighbourhoods with several weekly activities with large number of participants. A neighbourhood with GAME activities is defined as a GAME Zone, and thus a municipality with several low resource neighbourhoods may have several GAME Zones. Although some GAME Zones have been active for many years, GAME continuously seeks out possibilities for starting new GAME Zones. Further, some GAME Zones may be closed for a period or permanently, depending on a lack of recruitment of Playmakers, lack of facilities or lack of support from the neighbourhood. In May 2022, there were 105 educated and active peer leaders across 14 neighbourhoods (GAME Zones) in Denmark, responsible for a total of 28 weekly activities.

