### 2.3. The GAME Community Intervention

GAME Community is a holistic, complex community intervention. The main component of the intervention is the weekly peer-led street sport activities, which take place at a set time and place in low resource neighbourhoods across Denmark. The implementation of these activities is supported by five synergistic intervention components: (1) training of Playmakers, (2) a focus on inclusion of inactive girls and specific activities for this purpose, (3) parental involvement, (4) community engagement, and (5) organisational support. The components, described in more detail below, will be integrated and implemented stepwise into all neighbourhoods with GAME activities during 2021–2023. The components will take different forms in different communities to match the local context. The implementation of GAME Community is dependent on partnership building in the local communities and attracting and retaining volunteer Playmakers. Therefore, local adaptation and a flexible approach is necessary in both the implementation and evaluation of GAME Community. The logic model underpinning GAME Community is shown in Figure 1. The logic model was developed during ASPHALT 1 in a collaboration between research and GAME.

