#### 2.3.2. Inclusion of Inactive Girls

The Playmaker training has a general focus on how to ensure an inclusive attitude and approach, particularly towards girls. Further, a group of female Playmakers are trained specifically to facilitate a new multisport activity called GAME Girl Zone. The GAME Girl Zone concept was co-developed during ASPHALT I to specifically target inactive girls and focusses less on competition and more on social relations and co-determination in the sport activities.

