### 3.2. Sub-Study 2: Reach and Retention of Participants

For all GAME Zones, the degree of implementation of the GAME Community components will be assessed three times (in Fall 2021, 2022, and 2023), as the level of implementation at each GAME Zone is expected to either deteriorate or improve over time. Both scenarios are possible, although the intention is to achieve an increased implementation over time in all GAME Zones. Implementation degree is assessed by interviewing the regional GAME officers who oversee and support the implementation of GAME’s activities across all zones in Denmark. In 2021, comprehensive descriptions of the five GAME Community components were developed in collaboration between GAME and researchers. Based on these descriptions, the research team developed a structured interview guide to assess the implementation of the five GAME community components. For each GAME Zone, each component will be assigned a score from 1 (not implemented) to 5 (fully implemented). All GAME Zones will thus achieve a combined score between 5 and 25. By comparing GAME Zones with high and low implementation, we will explore the relationship between implementation of various programme components and programme reach in different contexts.

Simple registrations of all participants attending GAME activities across all GAME Zones will be collected from April 2022 using an app developed, managed, and owned by GAME. When a child attends an activity for the first time, the Playmaker will register the child’s attendance (activity and zone ID and date) in the app together with background information such as name, surname initials, gender, age, and current participation in organised leisure activities (assessed as current participation in sport, participation in other activities, or no current participation in organised activities). At all forthcoming GAME activities, recurring and new participant attendance will be registered. The app allows data to be linked if the same child attends different activities. Data from the app will handed over to research as an anonymised dataset. The participant registration data will allow for exploration of programme reach and retention of participants, including stratified analyses by, for example, current participation in organised leisure activities at first attendance. Moreover, registrations will provide insight into the number of activities and stability of activities over time.

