To understand relations between implementation of the GAME Community components and programme reach, retention and number and stability of activities, we will investigate the functioning of the intervention by considering the role of each component in the change process [35,40]. The participant registrations related to programme reach will further be combined with qualitative data of the perceived quality of the implementation and the functioning of the programme elements. These data will be collected as an integral part of the interviews conducted during Sub-study 1 (See Section 3.1). This will provide insight into the ways in which the GAME Community elements and contextual factors attract and retain participants, including girls who did not participate in sport prior to GAME participation.

The programme’s ability to attract and retain physically inactive girls will be explored in a qualitative study utilising ethnographic approaches. Girls participating in GAME activities will be followed by participant observation and interviewed during 2023. Girls will be recruited from the three GAME Zones with the highest participation of girls to provide insights on girls’ experiences of participating in GAME Zone activities, social interactions, and interaction with Playmakers.

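### GAME Girl Zone sessions, which belong to component 2, are not separated from the activity count that is related to component implementation

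*Protocol article*

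**What the plan says.** Section 2.3 lists component 2 as "a focus on inclusion of inactive girls and specific activities for this purpose". Section 2.3.2 describes it as a general emphasis on inclusion in Playmaker training and then adds that "a group of female Playmakers are trained specifically to facilitate a new multisport activity called GAME Girl Zone".

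Section 3.2 explains the scoring. Working from descriptions of the components, "the research team developed a structured interview guide to assess the implementation of the five GAME community components". Each component is scored 1 to 5 in each zone, and "All GAME Zones will thus achieve a combined score between 5 and 25".

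The same section takes the number of activities and their stability from app registrations, which cover attendance at activities in all zones and carry an activity identifier. It then states the purpose: "To understand relations between implementation of the GAME Community components and programme reach, retention and number and stability of activities". This is to be done by considering what each component contributes to change. No section treats Girl Zone sessions separately in the count.

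Section 2.2 gives the scale in May 2022: 14 zones, with peer leaders "responsible for a total of 28 weekly activities".

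**The concern.** The Girl Zone appears on both sides of one of the relations to be studied. It is part of what component 2 consists of, and it is also a weekly activity that the app counts. A zone that opens one may score higher on component 2 and, by the same act, show one more activity. A positive relation between component 2 and the number of activities could then appear even if implementation did nothing for any other activity.

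This would not be cured by better scoring. Section 4.2 acknowledges that the scores rest on the organisation's own appraisal, but a fully objective scorer would leave the overlap in place. At stake is whether a reader can tell that better-implemented zones sustain more activity overall, or only that they run the activity that forms part of the score.

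**Working it through.** The article states no sample size, power or correlation for this analysis, so there is no figure of its own to reproduce apart from the score range.

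**From the article**
- Combined score: five components scored 1 to 5 give 5 to 25, as stated. The range is 25 − 5 = 20 points. Component 2 spans 5 − 1 = 4 of them, one fifth.
- Activities per zone: 28 / 14 = 2.0. One added activity takes an average zone from 2 to 3, or +50%.

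Both the 4 points and the +50% are upper-end illustrations. The 4 points credit the whole of component 2 to the Girl Zone. The May 2022 count falls inside the 2021–2023 roll-out, so it may already include Girl Zones.

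**Illustration of the built-in correlation (assumptions not in the article)**
- 14 zones; other activities per zone distributed as 1 + Poisson(1), so mean 2 and variance 1.
- A proportion *p* of zones, 20% to 50%, runs a Girl Zone.
- Running it raises the component 2 score by *b* = 1 to 3 points, on top of a baseline uniform on 1 to 5 − *b*. The other four components are uniform on 1 to 5 (variance 2 each).
- It adds one activity. No component has any effect on the other activities.

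The covariance of component 2 with the activity count is then *b·p*(1 − *p*), so

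r = *b·p*(1 − *p*) / √[Var(C2) × Var(N)], with Var(C2) = [(5 − *b*)² − 1]/12 + *b²p*(1 − *p*) and Var(N) = 1 + *p*(1 − *p*).

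- Low end (*p* = 0.2, *b* = 1): 0.16 / √(1.41 × 1.16) = 0.16 / 1.279 = 0.125.
- High end (*p* = 0.5, *b* = 3): 0.75 / √(2.50 × 1.25) = 0.75 / 1.768 = 0.42.
- Combined score (add 4 × 2 = 8 to the score variance): 0.16 / √(9.41 × 1.16) = 0.05 and 0.75 / √(10.5 × 1.25) = 0.21.

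Simulation with 4,000 repetitions per scenario agrees: 0.12 to 0.43 for component 2 and 0.05 to 0.21 for the combined score. The three highest-scoring zones exceed the three lowest by 0.15 to 0.60 activities on average.

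**When it vanishes**
- If running a Girl Zone does not raise the score (*b* = 0), the correlation is 0.
- If the Girl Zone replaces another activity, the full count is unchanged and the correlation is 0.
- If the Girl Zone is added and its sessions are left out of the count, the correlation returns to 0 (within 0.01 in the simulation).

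One caution applies to the last step. Where a Girl Zone has replaced another activity, leaving it out lowers that zone's count by one. The covariance becomes −*b·p*(1 − *p*), an artefact of the same size with the opposite sign. Hence the need to show both counts.

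**The case against.** The strongest reply is that the overlap is inferred. The interview guide's items are not reproduced, which is normal for an article, and Section 2.3.2 puts general inclusive training first. Whether running a Girl Zone is scored, and how heavily, is unknown. The activity is called new, which does not mean additional. Both points stand, and they make the conclusion conditional.

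A reader might go further and infer that the score contains reach, retention and stability too. The documents do not support that. Opening a Girl Zone does not by definition bring in new children: few may come, or girls may move over from mixed activities. Reach may rise as a consequence, but that is an empirical matter. Section 4.1 specifies the implementation outcomes as reach and retention, so the degree-of-implementation question in Table 1 is not undermined as a whole.

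A reader might also want Girl Zone attendance removed from total or girls' reach. That would discard the effect component 2 is meant to have, since the activity was developed for inactive girls.

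Nor does the article claim that components cause the number of activities. It speaks of exploring relations, and Section 4.1 disclaims causal links between single components and behavioural or health outcomes. Even so, a descriptive association misleads if part of it is definitional.

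Finally, it may be said that such tabulations belong in an analysis plan. The component's definition and the list of outcomes are, however, both fixed in the article, and the overlap arises between them.

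**Conclusion.** The point holds in a limited form. Component 2 includes delivering a specific activity, the activity count covers all registered activities, and the two are to be related without separation. If a Girl Zone raises the component 2 score and adds to the schedule, part of the relation with the number of activities is built in.

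Under the assumptions shown, its size is small to moderate for component 2 and small for the combined score. Because Section 3.2 considers each component's role, the overlap is not confined to the diluted sum. It touches one of the four outcomes named there. The analysis is exploratory and the main outcomes lie elsewhere, so this is a cheap improvement of modest weight and no threat to the sub-study.

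**What to change.** - When implementation (component 2 or the combined score) is related to the number of activities, report the count both with and without Girl Zone sessions, identified by activity ID. Read the count without them as the relation that is not built in by definition.
- Note for each zone whether the Girl Zone was added to the schedule or took the place of another activity. Where it took the place of one, the count without it is too low by one and should be read beside the full count.
- Keep Girl Zone participants in total reach and girls' reach. Show reach and retention for Girl Zone and other activities side by side, so that any benefit of the Girl Zone stays visible as delivery of component 2.

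The cost is one extra tabulation from fields already in the app, plus one note per zone that can be taken at the scoring interview. The relation reported for the number of activities is likely to be weaker.

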### 3.3. Sub-Study 3: The Health Enhancing Potential of GAME Community

To have a health promoting effect, participation by children and youth should be continuous, and activities should be characterised by a moderate to vigorous activity level and/or pro-social behaviours. To investigate whether GAME Community activities have these characteristics, an observational study will be conducted. Data will be collected using structured observations across all activities that comply with being in a public open space and with a mean of at least five participants to ensure anonymity. Data on each of GAME’s activities that adhere to this standard will be collected at four time points: twice during spring 2022 and twice during fall 2022. We will use a combination of the validated systematic observation procedures SOFIT (System for Observing Fitness Instruction Time) [41] and SOCARP (System for Observing Children’s Activity and Relationships during Play) [42], both of which use momentary time sampling as an observation approach. SOFIT was developed for a physical education context while SOCARP was developed for observing playground settings. The two procedures use a similar observation technique and have several similar observation elements (e.g., physical activity level and activity content) and can therefore be used in combination. To maintain a manageable instrument, we will select the observation elements from each protocol which are most pertinent to our aim of assessing physical activity level and social interactions at the activity level. Using SOFIT and SOCARP, we will assess (a) physical activity level among participating children, (b) participants’ social behaviour and interactions, (c) GAME activity context and (d) features of the physical context, e.g., accessibility and amenities. An estimated total of 15–20 weekly GAME activities will be observed four times. Observers will be trained in accordance with SOFIT and SOCARP protocols [43,44]. Findings from these systematic observations will be analysed to characterise GAME activities in terms of their physical activity content and the children’s physical activity level and the degree to which they are characterised by pro-social behaviour. Observation data will be compared with participant registrations (see Section 3.2) from the included GAME Zones to explore patterns in activity characteristics and to explore characteristics of participants who are reached and retained.

## 4. Discussion

This study protocol presents how we will evaluate the functioning, reach, and outcomes of the GAME Community intervention using a multi-method design including three linked but independent studies. The results will provide unique insights into how and if children living in low resource neighbourhoods can be engaged and retained in physical activity through participation in peer-led, community-based sport.

### 4.1. Importance of This Study

It is important to evaluate the health enhancing potentials of practice-based interventions to determine if scarce societal resources are to be prioritised towards an intervention. In the case of GAME Community this is challenging, as individual level health outcomes cannot easily be assessed. Instead, we propose to evaluate intermediate health outcomes [45] of GAME Community (in terms of physical activity level and social behaviour and interactions) at an aggregated activity level using systematic observations. Further, we will synthesise data to evaluate implementation outcomes [38] in terms of reach (number of previously inactive children attracted, total number of children that participate and their retention) at an individual level using anonymised participant registration. Using this novel combination, the results will provide an indication of the health enhancing potential of the programme by establishing whether the participating children are attracted and retained in activities characterised by physical activity and positive social relations.

GAME Community is a complex health promotion intervention characterised by several interacting components that are delivered on several levels [37,46]. Further, for Playmakers and trainings to be successful, GAME Community needs to be implemented in a supportive environment. As such, context is part of the essence of GAME Community, with the programme both *relying on* [… a positive and supportive…] *context* to be a success but at the same time also *altering the context* by forming new partnerships between stakeholders in the neighbourhood and forming relationships among parents [36]. In sum, it is neither possible nor relevant to deconstruct a health promotion intervention such as GAME Community into its components and establish causal relationships between each component and behavioural or health outcomes, and an evaluation and research design that focuses only on internal validity, such as randomised trials, is ill-suited as a research framework in this community-based study. With an increased awareness of the pitfalls of applying strict controlled scientific study designs in evaluating complex public health interventions, recognition is growing that studies that engage with questions beyond the efficacy and effectiveness of complex interventions can provide important insights for research and practice [32,37]. With this in mind, this study protocol presents research initiated to evaluate the implementation, outcomes, reach, and functioning of a peer-led, community-based street sport intervention implemented at scale in low resource neighbourhoods, with a particular lens looking at girls.

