## 1. Introduction

Physical activity is important for children’s health in the short-term [1,2], as well as in the long-term, since physical activity behaviour tends to track from childhood and adolescence into adulthood [3]. Worldwide, only one out of five children adhere to international recommendations [4] and across high income countries there is inequality in physical activity with children from low socioeconomic status (SES) families being less physically active [5]. Increasing physical activity among children from low SES backgrounds is thus an important public health challenge [6], also contributing to reducing inequalities in health.

Different domains for children’s physical activity exist; recreation, transport, school, and household [7]. In the current study we will focus on recreational physical activity since participation in organised sport has proven to contribute to children’s physical activity [8] and further, sports club participation can be an important arena for children’s socialization experiences and social integration into the local community [9,10]. However, sports participation is influenced by the social environment in which children grow up, e.g., a recent systematic review and meta-analysis documented that the children living in low SES households participate less in sport [11]. Structural barriers to participation in organised sport for children from low SES families include: (i) fixed timetables for training, (ii) membership fees [9,12] and (iii) expectations of parent engagement [13]. Particularly girls from low SES families perceive barriers for participating in organised sport [12,14]. To redress inequality in sports participation among children, it is important to pay attention to alternatives to traditional sports club participation to attract and retain children from low SES families in being physically active [14,15].

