## Figures and Tables

**Figure 1 ijerph-19-15271-f001:**
[figure not shown]
Logic model for the GAME Community Intervention.

**Table 1 ijerph-19-15271-t001:** Sub-studies in the ASPHALT II evaluation.

Sub-Study	Research Question	Design and Methods	Population	Data	Time
**1. Functioning of the intervention *(activities and outputs)***	What is the functioning of the GAME Community programme?	Qualitative interviews and focus groups	Playmakers, parents, community stakeholders from 6 GAME Zones with varying implementation scores	Participants’ perceptions of the implementation and impact of the five GAME community components	2023
**2. Reach and retention of participants *(implementation outcomes)***	What is the relationship between degree of implementation and implementation outcomes?	Structured interviews with regional GAME officers and longitudinal participant registration	All GAME Zones	Each of the five GAME community components will be assigned a score from 1 (not implemented) to 5 (fully implemented) and combined with app data	Time 1: 2021, Time 2: 2022, Time 3: 2023
	What are the relations between implementation of the GAME Community components and programme reach and retention?	Qualitative interviews, focus groups and longitudinal participant registration	Playmakers, parents, community stakeholders from 6 GAME Zones with varying implementation scores	Participants’ perceptions of the implementation combined with participant registrations (app) on: gender, age, participation in other leisure activities, number of GAME activities attended	2022–2023
	Which components of the programme contribute to engage and retain girls in GAME activities?	Ethnographic field study	Girls who are active in GAME Zones with a high degree of girl participation	Participating girls’ experiences of participating in GAME activities, social interactions and interaction with peer leaders	2023

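### The 'previously inactive children' component of reach comes from an app item on organised leisure participation, which does not measure physical inactivity

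*Protocol article*

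**What the plan says.** Section 4.1 of the protocol article sets out the implementation outcome as "reach (number of previously inactive children attracted, total number of children that participate and their retention", and states that it is evaluated "at an individual level using anonymised participant registration". Reach is named in the primary objective in Section 2.1.

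Section 3.2 describes the registration. At a child's first attendance the Playmaker enters background information, including "current participation in organised leisure activities (assessed as current participation in sport, participation in other activities, or no current participation in organised activities". Table 1 lists the app variables for Sub-study 2 as "gender, age, participation in other leisure activities, number of GAME activities attended".

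Section 3.2 also gives an example of how the item will be used: "stratified analyses by, for example, current participation in organised leisure activities at first attendance". In describing the link between registrations and interviews, the same section refers to participants "including girls who did not participate in sport prior to GAME participation". It then assigns the attraction and retention of physically inactive girls to an ethnographic study.

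**The concern.** The outcome is named for a child's physical activity before joining. The field behind it records membership of organised leisure. These groups overlap but are not the same, and the article gives no rule that links them.

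Reaching inactive children, and girls in particular, was a stated purpose in developing the programme (Section 1). Section 4.1 introduces the evaluation by reference to how scarce societal resources are prioritised. A reported number of previously inactive children would be taken at face value by readers deciding on that basis, although the instrument supports only a statement about organised participation.

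**Working it through.** The document gives no counts and no figure for agreement between organised participation and physical activity, so there is nothing to recalculate. The check traces the outcome to its data.

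1. **Outcome.** Previously inactive children attracted, one of three components of reach (Section 4.1).

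2. **Source.** Individual app registrations (Section 4.1). The SOFIT/SOCARP observations cannot supply it. They record behaviour during GAME sessions (Section 3.3) at an aggregated activity level (Section 4.1), not what each child did before joining.

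3. **Field.** Of the fields described in Section 3.2 and Table 1, only the organised leisure item bears on activity outside GAME. It has three categories and carries no frequency, duration or intensity. It records current status at first attendance, which also has to stand in for 'previously'.

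4. **Construct.** The Introduction distinguishes four domains of children's physical activity, "recreation, transport, school, and household", and then declares a focus on recreation. Even within recreation, organised participation is only a part. A child who plays street football informally every day falls in the 'none' category. A child with one organised sport session a week falls in the 'sport' category, however little else they do.

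5. **Coding.** Let S, O and Z be the numbers of registered children in sport, other organised activities and none, so that the total is S + O + Z.
   - If 'inactive' means no organised activities, the count is Z.
   - If 'inactive' means no sport, as in "including girls who did not participate in sport prior to GAME participation", the count is O + Z.
   - The difference is (O + Z) − Z = O, the whole 'other activities' group.

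   The article does not say which reading Section 4.1 intends, or what falls under 'other activities'.

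6. **Bounds.** Neither count bounds the number of children who really were inactive. Active children in Z make Z too large. Inactive children in S are missed under both readings.

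7. **Caveat.** Section 4.2 discusses the restriction of observations to public open spaces, the risk of cancelled activities and the subjectivity of implementation scoring. It does not mention this proxy.

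**The case against.** The strongest reply is that this is a loose phrase in one parenthesis of the Discussion, while the Methods are accurate. Much of that stands.

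- **The example stratification is correctly labelled.** A reader might infer that the planned retention strata are misclassified by inactivity. The document does not support this: Section 3.2 names its example stratum by what is recorded. The problem would arise only if such strata were later reported as 'inactive'.
- **The scope is declared.** The Introduction states a recreational focus, and Section 4.2 says the programme is one part of total activity. Leaving out transport, school and household activity is therefore weak evidence against the item. Informal play lies within recreation, so that example survives.
- **It is not the main outcome.** A reader might take this as a flaw in a headline or primary endpoint. It is one of three components of reach. Section 2.1 names reach but not inactive children, and inactive girls are studied qualitatively.
- **The article is condensed.** Section 3.2 introduces the fields as examples, so the list is formally open, and a coding rule could sit in a fuller document. However, the article itself fixes both the outcome's name and its source, and neither Section 3.2 nor Table 1 shows a field that measures activity. The mismatch is in what is stated, not in what is left out.

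A reader might also try to size the error from the Introduction's statement that one in five children worldwide meets activity recommendations. That would require treating inactivity as falling short of recommendations, which the article never does. It would also apply a worldwide rate to Danish low resource neighbourhoods and assume both the share of registered children in organised sport and how activity differs between groups. None of these is given.

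**Conclusion.** The point holds as a mismatch between an outcome's name and its instrument. Followed as written, the study would report a number of previously inactive children that the described registration cannot establish. The effect is confined to that component of reach and to any app-based stratum or conclusion that borrows the word 'inactive'. Total participation is unaffected, and so is retention overall or by organised leisure status.

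The amount of misclassification is unknown and cannot be derived from the document. What can be said is that the choice between the two readings moves the count by the full size of the 'other activities' group. The conclusion assumes that the organised leisure item is the source of the count. The article does not say so outright, but it names the registrations as the source and describes no other field that could serve. The change is worth making because a component of reach is misnamed and renaming it costs almost nothing.

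**What to change.** 1. In Section 4.1, replace the reference to previously inactive children with 'children not participating in organised sport at first registration'. Define this as the 'other activities' and 'none' categories together, with 'none' also shown separately. This brings Section 4.1 into line with the labelling already used in Section 3.2.
2. Use the same label for any retention or girls' strata drawn from the app.
3. Draw no conclusions about 'inactive' children from this item.
4. In Section 4.2, state as a limitation that organised participation is a proxy and does not capture informal activity.

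The cost is a less striking claim; no new data are needed. Adding an activity question to the app is not recommended. Registration began in April 2022, so the answer would be missing for children already registered, and it would rest on an untested item collected by volunteer Playmakers.
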